## Abstract

**Background:**

Breastfeeding has a great effect on health promotion and disease prevention in premature infants. However, various factors affect the success of breastfeeding process in mothers. The present study aims to: a) explain breastfeeding experiences; b) assess the factors affecting breastfeeding self-efficacy; and c) present a guideline for promoting breastfeeding in mothers of premature infants.

**Methods:**

This mixed-methods study with a sequential explanatory design consisted of three phases. The first phase is qualitative study to explore the breastfeeding experiences in mothers of premature infants. In this phase, the subjects will be selected through purposive sampling; moreover, in-depth individual interviewing will be used for data collection. Finally, the conventional content analysis approach will be employed for data analysis. The second phase is quantitative and will be used a cross-sectional approach to assess the association of the social determinants of health with breastfeeding self-efficacy in mothers of premature infants. In this phase, the multistage cluster sampling method will be used to select 360 subjects who will be visited healthcare centers in Tabriz, Iran. The third phase focused on developing strategies to increase the ability of mothers to breastfeed their premature infants, using the qualitative and quantitative results of previous phases, a review of the related literature, and the nominal group technique will be performed among experts.

**Discussion:**

The present research is the first study that investigated the experiences of breastfeeding and factors influencing breastfeeding self-efficacy in mothers of premature infants. For the purposes of the study, the mixed methods approach will be used which aimed to develop strategies for the improvement of healthcare services in this regard. It is worth noting that there is no strategic guideline in Iran’s healthcare system for the improvement of breastfeeding, especially regarding mothers of premature infants. Therefore, it is hoped that the strategy proposed in the current study can lead to improvements in this regard.

**Ethical code:**

IR.TBZMED.REC.1398.100.

## Plain English summary

Breastfeeding confers crucial health benefits to both mothers and their babies. Unfortunately, the prevalence and duration of breast milk supply among premature infants tend to be lower than that of full-term infants. The current study provides precise information about the breastfeeding experiences of mothers of premature infants, and the factors influencing them. This study will be used the mixed methods approach with the sequential explanatory design and is comprised of three phases. The first phase is qualitative and explored the views of mothers. The second phase is quantitative and will be used a cross-sectional approach to assess the factors affecting the breastfeeding self-efficacy in mothers of premature infants in Tabriz. The findings of the qualitative and quantitative phases, the literature review, and nominal group technique will be used to establish some strategies to improve and promote breastfeeding practices. The strategy which is proposed by this study may be helpful to increase the ability of breastfeeding and promote health in premature infants.

## Introduction

Breast milk protects one’s health in childhood [1, 2] and also provides health and wellness for the rest of one’s life [3]. The importance of breastfeeding in various respects has been well recognized [4] It has protective effects on maternal and neonatal health, prevents multiple diseases and complications, and as a result reduces healthcare costs [2, 5], Moreover, it helps establish an attachment between a mother and her infant and is a good strategy for the reduction of infant mortality [6]. Many national and international organizations emphasize the importance of breastfeeding [7, 8]. For instance, according to the American Academy of Pediatrics, breastfeeding during the first 6 months is crucial for all the infants, especially premature ones [9] since they have a higher risk of death, complications, and behavioral problems, compared to the term infants [9–11]. These infants require special care and attention, and since they are prone to acute and chronic diseases, breastfeeding is more crucial for them [10]. The data suggest that breastfeeding is more beneficial for these infants and plays an important role in the development of their immune and cognitive systems [8, 12]. However, research has shown that preterm infants are more at risk of not receiving enough milk and that the rate of breastfeeding success in mothers of preterm infants is lower than that in mothers of term infants [5, 10]. This can be due to the fact that these mothers have a vulnerable and fragile situation which can affect their breastfeeding [5]. Moreover, malnutrition due to the lack of knowledge or attitude in mothers of these infants can exacerbate their problems, such as cardiopulmonary instability, premature fatigue during feeding, excessive irritability, prolonged sleep duration, have been reported which are more frequent in them than term neonates [12]. Ultimately, these infants are at higher risk of weight loss and developmental disorders during the early infancy period [13]. Empowerment plays a key role in the promotion of breastfeeding and the identification of the factors that can help improve breastfeeding practices [7]. Previous research suggests that multiple factors can be effective in initiating lactation and continuing the successful breastfeeding process [14–16]. In this regard, the researchers have examined the impact of socioeconomic status, physical-psychological status, social support, and self-efficacy. Given the results of these studies, it seems that any of these factors as social determinants of health can have a positive or negative effect on breastfeeding [8, 16, 17]. These factors are especially highlighted in mothers of preterm infants since they face additional obstacles leading to the delayed onset of breastfeeding [1]. Furthermore, studies show that mothers of preterm infants have lower socioeconomic status, compared to mothers of term infants which, in turn, can have negative effects on breastfeeding [16, 18]. In addition, breastfeeding self-efficacy of women is influenced by their perception of social support as well as their physical and mental status [8]. Therefore, it can be said that a number of different factors contribute to breastfeeding success [10, 19]. One of the strategies for achieving breastfeeding success is focusing on the affective factors; however, the experience of breastfeeding after preterm delivery has not been studied well [1, 10]. Addressing this knowledge gap is very important in the context of caring and support planning. Therefore, research in this field is of particular importance and can be helpful in understanding breastfeeding behavior. Such studies should examine the attitudes and beliefs, affective physical-psychological factors and social norms, and barriers regarding breastfeeding. The present research was designed to explore the factors affecting breastfeeding in mothers of preterm infants and their experiences. Moreover, this study aimed to investigate the impact of social determinants of health on breastfeeding self-efficacy.

### Objectives

The objectives of each phase are as follows:

### Objectives of the first phase: qualitative study

To explore breastfeeding experiences among mothers of premature infantsTo explore views about barriers and facilitators of breastfeeding in mothers of premature infants

### Objectives of the second phase: quantitative study

To determine Socio-economic situation among mothers of premature infants.To determine perceived social support among mothers of premature infants.To determine Psychological factors among mothers of premature infants.To determine breastfeeding self-efficacy in mothers of premature infants.To determine the association between Socio-economic situation with breastfeeding self-efficacy.To determine the association between perceived social support with breastfeeding self-efficacy.To determine the association between Psychological factors with breastfeeding self-efficacy.

### Objectives of the third phase

To develop Strategies to increase the ability of breastfeeding among mothers of Premature infants

## Methods/design

### Study design

A mixed methods sequential explanatory design will be used to conduct this study by collecting, analyzing, and integrating the qualitative and quantitative data. The mixed-methods paradigm is based on the principles and logic of pragmatism. According to this paradigm, the mixed use of qualitative and quantitative approaches results in a better understanding of the problem [20, 21]. This study will have three phases, and the qualitative and quantitative data will be collected in the first and second phases, respectively. Phase one is an exploratory qualitative study to explore breastfeeding experiences of mothers of premature infants in more detail. Phase two is cross-sectional study to assess the factors affecting the breastfeeding self-efficacy in mothers of premature infants. Phase three is about developing an evidence based and culturally sensitive guideline based on literature review, the results of phase one and two and experts’ opinion using the nominal group technique (Fig.1).

**Fig. 1 Fig1:**
[figure not shown]
Study diagram

### First phase: qualitative study

First Phase is an exploratory qualitative study with a conventional content analysis approach to explore experiences breastfeeding and views about barriers and facilitators of breastfeeding in mothers of premature infants.

### Sampling method

The research participants will be selected through purposive sampling among mothers of premature infants. Inclusion criteria including: having Iranian nationality and Resident in Tabriz, Ability to understand and convey concepts to the researcher, Mothers who give birth between 28 and 37 gestational weeks, having a history of at least 1–2 months of breastfeeding, having the tendency and ability to express and transfer concepts, with considering the maximum variability in terms of factors such as education, age, socioeconomic status. The withdrawal and non-attendance of the patient were considered as the exclusion criteria.

### Data collection

Qualitative data will be collected using in-depth and semi-structured interviews, containing open questions. Before conducting the interviews, the research team reviews the questions, and the ways to obtain valid data and focus on research questions. The interviewer will pilot the interview on a subset of participants, and used this information to further refine the guide with respect to culturally sensitive and appropriate questions. The interview will begin with a key question, “What were your experiences and feelings about feeding your premature infant?”. Then, the interview will continue by presenting other questions, such as “How do you cope with the difficulties of breast-feeding your baby?”, “What do you think about breastfeeding support? Have you received support?”, “What factors, in your opinion, can be helpful in breastfeeding?” and “What factors do you think may hinder your lactation?”. The interview will continue with more in-depth items, such as “what do you mean? Why? Can you explain further? Can you give an example?” to explore the depth of their experience. During the interview, as far as possible, the Note field will be used and non-verbal data such as tone of voice and behaviors were recorded, too. The sampling will continue until data are saturated. All interviews will be carried out in care centers in a quiet room and without someone other than the interviewees.

### Data analysis

Data analysis process will be performed simultaneously with data collection using MAXQDA software version 10. The qualitative data will be analyzed using qualitative content analysis based on the Graneheim and Lundman method [22]. In this approach, the data will be analyzed through frequent text reading to obtain a full understanding of it. Then, the texts will be read word by word to extract the codes. First, the objective words that contain the key concepts will be specified. The researcher continued digging the text by taking notes from the initial analysis until the major codes will be extracted. In this process, the code labels reflecting more than one key thought will be directly extracted and specified. Then, the codes will be categorized based on their difference and/or relationships. The codes will be categorized into themes and main categories. Subcategories will be extracted based on differences and similarities.

### Validation

To validate the results, at first it will be tried to establish a friendly relationship with the participants. In order to increase the accuracy of the data and for verification of the accuracy of the data, after the registration, the interviews will be given to the participants to review and confirm their stated content and, if there will be any other content, it will be added to the data. Interviews will frequently read by the corresponding author of the paper; then, the text of the interviews with the extracted codes and categories will be shared with the colleagues and their comments will be used. External monitoring will be also used to increase the reliability. By providing the initial code derived from the analysis and examples of the extraction, as external observers, the concepts will be given to other researchers who will be not related to the study in order to determine whether they also will have a similar perception of the data or no.

### Second phase: quantitative study

First, a cross-sectional descriptive analytical study will be conducted to evaluate association of the social determinants of health with breastfeeding self-efficacy in mothers of premature infants.

### Sample size and sampling method

Based on a study conducted by Nego et al. [8], and a confidence coefficient of 95%, statistical power of 90%, standard error of the mean (SEM) of 0.05, mean values of 141.1, 69.3, and 8.3, and the highest standard deviations of 15.9, 9, and 4.6 regarding the breastfeeding self-efficacy scale, perceived social support, and psychological factors and depression the necessary sample sizes were calculated at 20, 26, and 240 subjects, respectively. Since the sample size based on psychological factors and depression was larger, it was selected as the sample size of the study. Regarding the cluster sampling method and a design effect of 1.5, the final sample size was estimated at 360 participants.

Sampling will be conducted in the healthcare centers in Tabriz. There are 82 public healthcare centers (*n* = 40) and posts (*n* = 42) in different regions of the city that provide primary care services, including postpartum care and infant care, free of charge. All the mothers and infants in Tabriz have health records in these healthcare centers and posts. A two-stage cluster sampling will be carried out so that 13 healthcare centers and 14 healthcare posts were selected using a randomizer software (www.random.org). A list of all breastfeeding mothers of premature infants at each center will be extracted from the health records and the samples will be randomly selected from the ordered numbers. Afterward, Using the phone number registered in each record, the researcher will call the potential participants and invite them to participate in the study. The eligible participants will be provided with full explanations about the study objectives and procedures. Also, informed consent will be obtained before collecting information, and be emphasized the importance of honest answers to the questionnaire, and asked them to complete the anonymous questionnaires in a private room. A number of participants are likely to be illiterate, so the questionnaires will be completed by the researcher in order for the data collection method to be the same for all individuals.

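### The sample size that sets phase 2 (240, then 360) does not follow from its printed inputs, 0.05 is mislabelled as a standard error, and the 90% power is attached to no effect

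*Protocol article*

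**What the plan says.** The section Sample size and sampling method takes its inputs from a cited earlier study. It states "a confidence coefficient of 95"%, then "statistical power of 90%, standard error of the mean (SEM) of 0.05", then "mean values of 141.1, 69.3, and 8.3" for breastfeeding self-efficacy, perceived social support, and psychological factors and depression. The SDs, in the same order, are 15.9, 9 and 4.6. From these, "the necessary sample sizes were calculated at 20, 26, and 240 subjects, respectively". No formula is named, and no separate margin is given for the third scale.

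The psychological scale is chosen because its figure is the largest. The text then concludes: "Regarding the cluster sampling method and a design effect of 1.5, the final sample size was estimated at 360 participants". The abstract repeats 360.

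The second-phase objectives are four descriptive aims and three association aims, one of them "To determine the association between Psychological factors with breastfeeding self-efficacy".

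**The concern.** One common set of inputs is said to give all three sizes. Two of them follow from a single simple formula and the third does not. The one that fails is the only one that matters: 20 and 26 have no influence on the study, while 240 fixes the final size. A reader would take the protocol to promise a 5% margin on the psychological score, and 360 does not deliver that with the printed mean and SD.

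The labels add to the difficulty. A precision calculation for a mean has no place for power, and a power figure means nothing without a difference, correlation or regression effect to detect. The paragraph gives none, although three of the seven objectives are associations.

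**Working it through.** **Inputs**, all from Sample size and sampling method: 95% confidence (taken as two-sided, z = 1.96), 0.05, the three means and SDs, and a design effect of 1.5.

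**Step 1. Reproduce the stated figures.** Read 0.05 as a margin of 5% of the mean: n = (1.96 × SD / (0.05 × mean))².

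| Scale | Calculation | Result | Stated |
|---|---|---|---|
| Self-efficacy | (1.96 × 15.9 / 7.055)² | 19.5, so 20 | 20 |
| Social support | (1.96 × 9 / 3.465)² | 25.9, so 26 | 26 |
| Psychological factors | (1.96 × 4.6 / 0.415)² | 472.0, so 472 | 240 |

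After the design effect, 472 × 1.5 = 708. The step 240 × 1.5 = 360 is correct arithmetic.

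**Step 2. Try other readings of 0.05 and of the power.**
- Literal standard error, (SD/0.05)²: 101,124, 32,400 and 8,464.
- Standard error of 5% of the mean, (SD/(0.05 × mean))²: 5.1, 6.8 and 122.9.
- 90% power added, replacing 1.96 by 1.960 + 1.282 = 3.242: 54, 71 and 1,291.
- One-sided 95%: 14, 19 and 333.

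None gives 20, 26 and 240 together. Only the 5% relative margin gives 20 and 26.

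**Step 3. Ask what would give 240.**
- A margin of 7% on the third scale: (1.96 × 4.6 / (0.07 × 8.3))² = 240.8. At 7% the other two scales would need 10 and 14.
- A 5% margin with SD 4.6 and a mean of about 11.6: 1.96 × 4.6 / (0.05 × √240) = 11.6.
- A 5% margin with mean 8.3 and an SD of about 3.3: 0.05 × 8.3 × √240 / 1.96 = 3.28.
- A finite population correction, n/(1 + (n − 1)/N), with N of about 488: 471.97/(1 + 470.97/488) = 240.2. Applied to the other scales it gives 18.8 and 24.7, that is 19 and 25, so it does not explain the set.

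**Step 4. What 360 delivers.** Effective n = 360/1.5 = 240, and √240 = 15.49. The 95% half-widths are:
- Self-efficacy: 1.96 × 15.9/15.49 = 2.01 points, 1.4% of 141.1.
- Social support: 1.96 × 9/15.49 = 1.14 points, 1.6% of 69.3.
- Psychological score: 1.96 × 4.6/15.49 = 0.58 points, 7.0% of 8.3.

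For a simple correlation tested two-sided at 5%, 90% power at effective n = 240 corresponds to r = tanh(3.2415/√237) = 0.21.

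**The case against.** The best counter-argument is that the formula is inferred and not stated. Two exact matches from two different mean and SD pairs make it very likely, but they do not show how 240 was obtained. The margin may have been relaxed to 7% for the third scale, or the mean or SD may be misprinted, and the cited study is not at hand to settle it. This stands: a reader might infer that 472 and 708 are the right numbers, but the document does not support that. For the same reason, the absence of power from the calculation is shown for 20 and 26 only. It is consistent with 240 under the 7% reading, but not proved.

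A reader might also infer that the study has neither its precision nor its power. That goes too far. Self-efficacy, the outcome, is estimated to 1.4% and social support to 1.6%, both well inside 5%; only the psychological score misses. Nor is the study shown to be underpowered for associations, since a correlation of about 0.21 is within reach.

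Finally, four of the seven objectives are descriptive, so sizing on the precision of means is a legitimate choice, and a condensed article need not give a detectable association. That also stands. The defect is narrower: the paragraph prints inputs and a result that disagree, and claims a power to which no stated effect belongs.

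**Conclusion.** The point holds. From the printed inputs, the formula that yields 20 and 26 yields 472 and not 240 for the scale that sets the study, and so 708 and not 360. This is about a factor of two and cannot be rounding. Which printed item is wrong (the result, the margin, the mean or the SD) cannot be told from the document. The label on 0.05 is wrong on any reading that fits the figures, and the 90% power does no work in 20 or 26.

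The practical damage is limited to the sample size justification. If the printed mean and SD are right, 360 gives a 7.0% margin on the psychological score in place of 5%, and adequate precision on the other two scales. This rests on a two-sided 95% interval, the normal approximation, and the protocol's own design effect of 1.5.

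**What to change.** Keep 360 and restate the paragraph:

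1. Name the formula and call 0.05 a relative margin of error, not a standard error of the mean.
2. Reconcile the third calculation against the source study, either by correcting the mean or SD or by declaring the margin actually used. If the printed inputs stand, report that 360 gives ±0.58 points (7.0% of 8.3) for the psychological score, with 1.4% for self-efficacy and 1.6% for social support.
3. Remove the 90% power from the precision calculation, or attach it to a stated association. For example, with the design effect of 1.5, 360 mothers give 90% power for a simple correlation of about 0.21 (two-sided 5%). Present this as what the chosen size can detect, not as the basis of the design. It covers a bivariate correlation only, not the group comparisons or the adjusted regression also planned.

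The cost is one paragraph and a check of the cited source, with no extra participants and no change to the analysis. The downside is that, if the printed mean and SD stand, the stated precision for the psychological score becomes less favourable.

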### Inclusion criteria

The inclusion criteria consisted of 1) Iranian nationality, 2) residency in Tabriz, 3) literacy, 4) infant age range within 28–37 weeks, 5) passage of 4–6 months after the preterm birth of the infant, 6) lack of disease and malformations of the infants, 7) no history of stressors in the last 6 months (e.g., divorce, death of a family member, and diagnosis of a family member with an incurable or life-threatening disease), 8) breastfeeding (exclusively or with auxiliary milk).

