### Scales and data collection

Quantitative data will be collected using 5 questioners, including:

**Sociodemographic characteristics questionnaire:** consisted of questions about the mother’s and father’s ages, the mother and father’s education, number of pregnancies, number of deliveries, pregnancy interval, gestational age at delivery, and the infant’s age and sex.**Socioeconomic Status Questionnaire:** This questionnaire had 19 questions about occupational status, level of education of the couple, residence, status of home ownership, the amount of rent or mortgage, house area, family economic status (evaluating eight items), family size, number of family members, ethnicity, insurance, receiving food aid, whether being supported by social organizations, monthly income, and total family expenditure. The economic status will be assessed as poor, average, and good by having less than 3 items, 4 to 6 items, and more than 7 items, respectively. The validity of the researcher-made socioeconomic questionnaire have been evaluated in Dolatian et al. study through content validity, and its reliability have been assessed using internal consistency, Cronbach’s alpha (0.876), and retest (0.916) [23].**Multiple Scale of Perceived Social Support Questionnaire (MSPS):** This is a social support questionnaire designed by Zimet et al. that encompasses 12 items scored based on a Likert scale. The questionnaire evaluates three domains of perceived support from the family (four items), perceived support from family members and acquaintances (four items), as well as perceived support from friends (four items). The items are scored based on a seven-point Likert scale from “completely disagree” (score: 1) to “completely agree” (degree: 7) in which the minimum and maximum scores are 12 and 84, respectively [19]. Total scores of answering the questions fall in three categories: Low (scores 12–48), Moderate (scores 49–68) and high (scores 69–84) social supports [24]. This instrument also has been validated in Iran by Bagherian-Sararoudi R et al., as Cronbach’s coefficient has been found to be 0.92 for the scale and 0.89, 0.92 and 0.87, for friends, significant others and family subscales, respectively [25].**The Depression, Anxiety and Stress Scale (DASS-21):** This is a 21-item questionnaire first presented by Love bound in 1995 that uses 7 questions to measure each of the symptoms of stress, anxiety, and depression. This questionnaire was designed as a Likert questionnaire. The lowest score for each question was a score of zero and the highest the score of 3. In each section related to anxiety, depression and stress, a score of 1–7 indicated a mild level, a score of 8–14 indicated a moderate level, and a score of 15–21 indicated a severe level of anxiety, depression and stress. This questionnaire has been used in various surveys and its validity and reliability have been confirmed [23].**The breastfeeding self-efficacy questionnaire**: It was designed by Dennis (2003). This questionnaire is a 33-item scale and is scored by a 5-point Likert scale from always confident (5) to not at all confident (1). Scores range from 33 to 165, with 33–76 considered low self-efficacy, 77–120 average self-efficacy, and 121–165 regarded as high self-efficacy. The reliability of this questionnaire was reported 82% in a study by Varaei et al. [26].

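### Phase 2 requires literacy, yet its procedure expects illiterate participants and has the researcher complete every form because of them

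*Protocol article*

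**What the plan says.** All of this concerns the second phase in the Protocol article.

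- **Eligibility (Inclusion criteria).** Literacy is the third criterion: "The inclusion criteria consisted of 1) Iranian nationality, 2) residency in Tabriz, 3) literacy".
- **Expected participants (Sample size and sampling method).** "A number of participants are likely to be illiterate, so the questionnaires will be completed by the researcher". The purpose given is "in order for the data collection method to be the same for all individuals".
- **Completion of forms (same section, the sentence before).** After consent, mothers are "asked them to complete the anonymous questionnaires in a private room".
- **Aim (Second phase: quantitative study).** To "evaluate association of the social determinants of health with breastfeeding self-efficacy in mothers of premature infants".
- **Objective (Objectives of the second phase).** "To determine the association between Socio-economic situation with breastfeeding self-efficacy". Describing the socioeconomic situation of these mothers is a separate objective in the same list.
- **Exposure measurement (Scales and data collection).** "This questionnaire had 19 questions about occupational status, level of education of the couple". The sociodemographic questionnaire also records both parents' education.

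**The concern.** An eligibility rule and a data collection procedure for the same phase assume different populations. Staff recruiting from the 27 selected sites (13 centres and 14 posts) could follow either, and the article does not say which prevails.

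The choice matters because this phase studies social determinants. A literacy requirement excludes mothers at the lowest end of education, which is one of the determinants measured. The description of socioeconomic situation would then cover literate mothers only, and correlations with breastfeeding self-efficacy would be computed over a restricted range.

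A smaller problem sits beside it. One sentence has mothers filling in the forms and the next has the researcher doing so. The intention can be guessed, but the wording does not state it cleanly.

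**Working it through.** The article gives no figure for this point, so the main check sets the texts side by side.

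**Step 1: can the two rules coexist?**

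| If the literacy criterion is... | Illiterate mothers enrolled? | Consequence |
|---|---|---|
| enforced | none | The expectation of illiterate participants is false, and the reason for researcher completion falls away |
| not enforced | some | Each such mother breaches the third inclusion criterion |

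Neither row agrees with both texts. The sampling section cannot mean candidates who are screened out later, because the sentence fixes how participants' questionnaires are filled in.

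**Step 2: does another section resolve it?** No. The exclusion criteria cover only incomplete questionnaires and unwillingness to continue. Phase 1 has no literacy criterion and seeks wide variation in education and socioeconomic status, so an enforced criterion would also make the quantitative phase narrower than the qualitative phase it is combined with in phase 3.

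**Step 3: what does enforcement do to the exposures?** The mother's own education loses its lowest level. The article does not list the education categories, but illiterate mothers would fall at the bottom of any. The father's education and the other items (housing, income, insurance and so on) are restricted only so far as they go with the mother's literacy.

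**Step 4: how large could the attenuation be?** The article gives neither an illiteracy rate nor an expected correlation, so every input here is an assumption: a true correlation r = 0.30, a normally distributed socioeconomic score, and 5% or 15% of mothers removed.

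With u the ratio of restricted to unrestricted SD of the score, r' = r·u / √(1 − r² + r²u²).

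- *Upper case: selection acts on the score itself.* Removing the lowest 5% gives u = 0.90 and r' = 0.30 × 0.90 / √(0.91 + 0.09 × 0.81) = 0.272. Removing the lowest 15% gives u = 0.80 and r' = 0.30 × 0.80 / √(0.91 + 0.09 × 0.64) = 0.244.
- *More realistic case: selection acts on a literacy trait correlated ρ with the score.* The SD ratio of the score is then √(1 − ρ²(1 − u²)). This assumes that literacy has no link with self-efficacy beyond the score.

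| Removed | ρ = 0.5 | ρ = 0.7 |
|---|---|---|
| 5% | r' = 0.293 | r' = 0.287 |
| 15% | r' = 0.287 | r' = 0.274 |

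The socioeconomic questionnaire has 19 questions across many domains, so the second case is the better guide. The loss there is about 0.01 to 0.03.

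**The case against.** The strongest reply accepts the contradiction and disputes how much follows from it. Most of that reply stands.

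- **Mode confounded with literacy.** A reader might infer that some mothers complete the forms themselves while illiterate mothers are interviewed, so that mode is confounded with education. The article does not support this. It chooses researcher completion so that one method applies to all. Nor can this harm occur together with truncation: truncation needs the criterion enforced, and then no illiterate mother is present for mode to differ by.
- **Self-completion against researcher completion.** The two sentences are adjacent, and the second can be read as saying how the first is carried out: the mother answers in a private room and the researcher fills in the form. This is loose wording to tidy, not a second contradiction of equal weight.
- **Bias in the association.** Selection on an exposure attenuates Pearson's correlation. It need not bias a linear regression slope if the relation is linear and selection depends only on that exposure, and the data analysis section plans regression as well as correlation.
- **Anonymity.** Researcher completion does not by itself defeat it, since a form without a name can still be anonymous.
- **Which text is the slip.** The article does not show whether the criterion or the illiteracy sentence is the mistake. Restricting to literate mothers is a legitimate, narrower population. So deleting the criterion is a preference with reasons, and the firm requirement is to reconcile the two.

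**Conclusion.** The contradiction is real and rests on the text alone: the inclusion criteria require literacy, and the procedure plans for participants who lack it. It affects who is enrolled and should be corrected, but it does not invalidate the phase.

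If the criterion is enforced, the lowest level of maternal education is excluded and the description of socioeconomic situation applies to literate mothers only. Correlations with self-efficacy may be modestly attenuated. The amount cannot be computed from the article; the figures of 0.27 to 0.29 for a true 0.30 are illustrations resting on assumed proportions removed and assumed correlations with literacy, and 0.244 is an upper case that treats literacy as if it were the socioeconomic score. If few mothers are illiterate, the effect is smaller still.

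**What to change.** Reconcile the inclusion criteria with the sampling section of phase 2.

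1. **Preferred: delete the literacy criterion.** Researcher completion for everyone is already planned, so literacy serves no purpose in data collection, and education keeps its full range. The cost is a slightly wider eligible population and a consent process that does not rely on reading, so this is more than a wording change.
2. **Alternative: keep literacy.** Delete the sentence expecting illiterate participants and limit the conclusions to literate mothers. The cost is narrower generalisability in a study of social determinants.
3. **In either case, state one mode of administration.** Replace the self-completion sentence. With researcher completion, say that the researcher reads the items and records the answers in a private room, on forms without names. This costs wording only.
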